### 2.2. Contextual framework

The study will be carried out within the framework of primary health care in the Spanish region of Aragon. Aragon is an Autonomous Community located in the northeast of Spain. It is the fourth Spanish Autonomous Community by territory but ranks 11 out of 17 in terms of population. It has a population of 1.3 million inhabitants: 60% live in urban areas (675,301 inhabitants live in the city of Zaragoza) and semi-urban areas and 40% of the remaining population lives in towns with fewer than 5,000 inhabitants. Aragon has an aging population, with 23.5% of people over 64 years of age. The average socioeconomic level of Aragon is medium, and the unemployment rate is lower than the national average. Public health provides assistance for nearly the entire population [around 70–85% of the population opts for public primary health care over private (59)]. Aragon public primary health care is structured into 8 health sectors organized into 123 Basic Healthcare Areas (BHA), which include 118 health centers and 870 local clinics (66, 67). Spanish primary health care is made up of a multidisciplinary team of general practitioners, nurses, psychologists, social workers, physiotherapists and occupational therapists.

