### 2.4. Sample size and sampling

The sample size was computed using the formula for caclulating the population estimates of the most prevalent affective disorders in primary care (anxiety and depression) (69). To calculate the sample size, we will use the data obtained in the study by Santomauro et al. (57). We used the prevalence of the most frequent affective disorders and addictions in primary care (anxiety, depression) as the main variable: 3.1% for major depression and 4.8% for anxiety disorders. Accepting an alpha value of 0.05 and a margin of error of 3% of units, the total sample size required was 290 with the expectation of a possible 30% withdrawal rate.

n=Zα2⁢p⁢(1-p)e2

For selecting potential participants, stratified selection will be made by age, sex and population distribution in urban and rural areas with respect to the National Institute of Statistics data from the census of Aragon 2021 (Figure 1 and Table 1). This stratification will be carried out with the intention of establishing the greatest variability within the sample and reaching a maximum level of representativeness for the population (Table 2). To achieve this, different primary care health centers in the autonomous community, 1–2 rural centers and 1–2 urban centers, will be selected. The rural centers sampled will be in towns with a population of under 2,000 inhabitants.

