**FIGURE 1 F1:**
[figure not shown]
Total population distribution of Aragon by age and sex respect to National Institute of Statistics data from the census of Aragon 2021.

**TABLE 1 T1:** Total population distribution in urban and rural areas of Aragon respect to National Institute of Statistics data from the census of Aragon 2021.

Province	Urban area, *n* (%)	Rural area, *n* (%)
Teruel	36,240 (27.01)	97,936 (72.99)
Zaragoza	701,969 (72.18)	270,559 (27.82)
Huesca	53,956 (24.23)	168,731 (75.77)
Total	792,165 (59.59)	537,226 (40.41)

**TABLE 2 T2:** Stratified selection of Aragon population by sex, age, and population distribution.

Years	Total			Rural (40.41%)			Urban (59.59%)		
	**Both**	**Men**	**Women**	**Both**	**Men**	**Women**	**Both**	**Men**	**Women**
35–39	49	25	24	20	10	10	29	15	14
40–44	59	30	29	24	12	12	35	18	17
45–49	58	30	28	23	12	11	35	18	17
50–54	55	28	27	22	11	11	33	17	16
55–59	52	26	26	21	11	10	32	16	16
60–64	46	23	23	18	9	9	28	14	14
65–69	39	19	20	15	7	8	23	11	12
70–74	36	17	19	18	7	8	21	10	11
Total	395	198	197	158	79	79	237	119	118

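### The rural quota and the choice of rural centres appear to rest on different town-size limits, and a 3-point margin calculated for independent individuals is not assured when everyone comes from 2–4 centres

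*Protocol article*

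**What the plan says.** **Rural definition.** Section 2.2 of the protocol article describes 60% of the population as urban or semi-urban and continues: "40% of the remaining population lives in towns with fewer than 5,000 inhabitants". Table 1, captioned "Total population distribution in urban and rural areas of Aragon respect to National Institute of Statistics data from the census of Aragon 2021", gives 792,165 urban and 537,226 rural residents and states no size limit for either class. Table 2 carries the resulting 40.41% forward as the rural quota, with a printed rural total of 158 out of 395. Section 2.4 then says of the centres: "The rural centers sampled will be in towns with a population of under 2,000 inhabitants".

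**Number of centres.** Section 2.4 says "1–2 rural centers and 1–2 urban centers, will be selected", so 2 to 4 in all. Section 2.2 counts 118 health centres in the region. The stated purpose of the stratification is to make the sample as representative of the population as possible.

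**Sample size.** Section 2.4 uses the single-proportion precision formula with prevalences of "3.1% for major depression and 4.8% for anxiety disorders" and the condition "Accepting an alpha value of 0.05 and a margin of error of 3% of units". It arrives at 290, allowing for 30% withdrawal. No design effect or intraclass correlation appears.

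**Models.** Section 2.7 admits to the regressions only variables that were significant in bivariate analysis, and then removes variables stepwise.

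**The concern.** Two features of the sampling do not fit the figures built on it.

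First, a quota stands for the population whose share it carries. If the 40.41% counts everyone in towns under 5,000 but rural places are filled only through centres in towns under 2,000, the smallest towns carry the weight of a broader group. Residents of towns of 2,000–5,000 are counted in the quota without any stated route into the sample.

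Second, people who attend the same centre share local care and living conditions, so their outcomes may be correlated. A formula for independent individuals then overstates precision, and the effect grows with the number of people per centre, which is large here. If only one centre per area type is used, any rural/urban difference is also a difference between two particular centres.

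At stake are the sample size rationale and the claim to represent Aragon. To a lesser degree, so is the main regression analysis, where centre differences could confound the associations.

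**Working it through.** **1. The plan's own figure.** n = Z²p(1−p)/e², with Z = 1.96 (two-sided 0.05) and e = 0.03 read as absolute points.
- p = 0.048: n = 195.0, rounded up to 196; 196/0.7 = 280.
- p = 0.031: n = 128.2, rounded up to 129; 129/0.7 rounds up to 185.
- p = 0.05 (not stated in the plan): n = 202.7, rounded up to 203; 203/0.7 = 290.

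So 290 follows from a prevalence rounded to 5% but not from either stated value. Below, 290 is taken as the number recruited, 203 as those left after 30% loss, and 395 as the Table 2 allocation.

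**2. The rural share.** 537,226/(792,165 + 537,226) = 537,226/1,329,391 = 40.41%. This agrees with the 40% that Section 2.2 attaches to towns under 5,000. The document gives no share for towns under 2,000. Read literally, the Section 2.2 sentence would mean 40% of the remaining 40%, or 16% of the total. The natural reading is the remaining 40%, and only that reading agrees with Table 1.

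**3. Margin without clustering.** 1.96·√(p(1−p)/N) at p = 0.048 gives 2.94 points for 203, 2.46 for 290 and 2.11 for 395. All meet 3 points.

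**4. Margin with clustering.** Design effect = 1 + (m − 1)·ICC, with m = N/number of centres (equal sizes assumed). The margin is the step 3 value times √(design effect). The plan gives no ICC, so 0.005–0.02 is an assumption. Example: 203 people in 4 centres, m = 50.75, ICC 0.005 gives a design effect of 1.25 and 2.94 × √1.25 = 3.29.

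| N | 4 centres, ICC 0.005 to 0.02 | 2 centres, ICC 0.005 to 0.02 |
|---|---|---|
| 203 | ±3.29 to ±4.15 | ±3.60 to ±5.10 |
| 290 | ±2.87 to ±3.84 | ±3.23 to ±4.85 |
| 395 | ±2.57 to ±3.62 | ±2.97 to ±4.68 |

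At p = 0.031 the margins are smaller:
- 203 people: ±2.66 to ±3.37 (4 centres) or ±2.92 to ±4.14 (2 centres).
- 395 people: ±2.09 to ±2.94 or ±2.41 to ±3.80.

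**5. ICC above which 3 points is missed** (p = 0.048; 4 centres / 2 centres).
- 203: 0.0008 / 0.0004.
- 290: 0.0068 / 0.0034.
- 395: 0.0105 / 0.0052.

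As N grows, the margin tends to 1.96·√(p(1−p)·ICC/number of centres). With 2 centres and ICC 0.02 that floor is 1.96·√(0.045696 × 0.01) = 4.2 points, so no sample size reaches 3.

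**6. Coverage.** The bias in a prevalence is the uncovered share times the difference in prevalence. The document gives neither. Assuming a share of 5–20% and a difference of 1–5 points, it is 0.05 to 1.0 points.

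**7. Separating centre from area type.** Two centres give one degree of freedom between centres, and the rural/urban contrast uses it. Four centres give three: one for rural/urban and two within area type.

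**The case against.** The other side has a good deal to say.

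- **Table 1 gives no cut-off.** The 5,000 figure stands only in the description of the setting, in an awkward sentence. This stands: the tie to 40.41% is an inference, though the matching split makes it a strong one.
- **A reader might infer that people in towns of 2,000–5,000 can never be sampled.** The text does not support that. Section 2.4 limits where the centre lies and does not restrict where its patients live. Catchments are not described, and Section 2.5 adds recruitment through general media. What remains is that the plan does not show how these towns are covered.
- **A reader might infer that the 3-point margin is missed.** That depends on an ICC the document does not give. With 395 people and an ICC of 0.005 it is met, just, even with two centres.
- **A reader might scale the nominal 3.0 points by the design effects for 395 people, which gives about ±3.7 to ±6.7.** That mixes two sample sizes: 395 people start from 2.11 points.
- **The main objective is association by regression, so the prevalence margin matters mostly for the sample size rationale.** This stands, and it limits the consequence.
- **A centre term may be specified in an analysis plan that is not shown.** Its absence from the article is therefore no fault in itself. However, the entry rule in Section 2.7, applied as written, would keep centre only if it happened to be significant. The heteroscedasticity correction planned there for the mediation and moderation analyses does not deal with correlation within centres.

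**Conclusion.** The concern holds in a limited form. The document uses two town-size limits for the small-town population, 5,000 and 2,000, without reconciling them. The 40.41% quota matches the share given with the wider limit, while the rural centres follow the narrower one. The resulting bias cannot be sized from the document.

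The 3-point margin is not assured. At 203 people there is almost no reserve, and any ICC above 0.0004–0.0008 exceeds it. The baseline estimate uses all those recruited, so 290 or 395 is the fairer basis there, and the margin then holds at small ICCs and fails at larger ones. These figures rest on the assumed ICC range, 4.8% prevalence and equal centre sizes.

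With one centre per area type, which the plan permits, centre and rural/urban cannot be separated by any later analysis.

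**What to change.** 1. Use one rural definition for both the quota and centre eligibility. Either align the centre limit with the definition behind the 40.41%, and state that definition under Table 1, or recompute the rural share and the Table 2 quotas for towns under 2,000.
2. Fix the number at two centres per area type, which is already within the plan.
3. Restate the margin of error with a declared design effect, and say that its ICC is assumed. Four centres will give little information on it.
4. Keep centre as a fixed effect in the regression models whatever its bivariate significance. Note that it absorbs the rural/urban contrast and does not repair the prevalence margin.

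The cost is some rewording, possibly a recomputed Table 2, a less favourable stated margin and up to three degrees of freedom per model. Where the plan would have used only one centre of a type, there is also the work of running a second.

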**FIGURE 1 F1:**
[figure not shown]
Total population distribution of Aragon by age and sex respect to National Institute of Statistics data from the census of Aragon 2021.

**TABLE 1 T1:** Total population distribution in urban and rural areas of Aragon respect to National Institute of Statistics data from the census of Aragon 2021.

Province	Urban area, *n* (%)	Rural area, *n* (%)
Teruel	36,240 (27.01)	97,936 (72.99)
Zaragoza	701,969 (72.18)	270,559 (27.82)
Huesca	53,956 (24.23)	168,731 (75.77)
Total	792,165 (59.59)	537,226 (40.41)

**TABLE 2 T2:** Stratified selection of Aragon population by sex, age, and population distribution.

Years	Total			Rural (40.41%)			Urban (59.59%)		
	**Both**	**Men**	**Women**	**Both**	**Men**	**Women**	**Both**	**Men**	**Women**
35–39	49	25	24	20	10	10	29	15	14
40–44	59	30	29	24	12	12	35	18	17
45–49	58	30	28	23	12	11	35	18	17
50–54	55	28	27	22	11	11	33	17	16
55–59	52	26	26	21	11	10	32	16	16
60–64	46	23	23	18	9	9	28	14	14
65–69	39	19	20	15	7	8	23	11	12
70–74	36	17	19	18	7	8	21	10	11
Total	395	198	197	158	79	79	237	119	118

### 2.5. Data collection

The research team will perform an information session about the study at the selected health centers. In these sessions, the research team will explain the project to be carried out and its methodology to all primary care professionals (family doctors, nurses, psychologists, social workers, physiotherapists) who work in the selected health centers. With these informative sessions for PHC professionals and a good line of contact established with the research team, the aim is to ensure and improve the recruitment rate since PHC professionals maintain good and trustworthy contact with the population. They will also be provided with the telephone number of the research unit for the initial appointment if any patient that these professionals receive in their daily work is interested in participating in the study.

The research team will send an information letter to the participants obtained from the stratified sampling. This letter will include information on the study procedure and contact details of the research unit, so participants who are interested can contact the research team. All members of the multidisciplinary research group come from primary health care and public health.

In addition, broadcasting will be carried out through general media, posters, and press releases, which will raise awareness and obtain greater data at the beginning of the study. Patients who will be interested in the study will arrange a meeting with the research team at their health center to explain the study in more detail, verify that they meet the inclusion and stratification criteria and sign the informed consent if they wish (Supplementary Material 2). All researchers will be trained to conduct research in a systematic and unified method for data collection. A research assistant will collect the data, and another will enter and encode the data into a database. All subjects’ data will be anonymized and will only be used for the purposes of the study. To maintain anonymity, researchers who manage the data of the database or who perform the evaluation of the results and the analysis of the data will not know or have access to data that would allow them to identify the patient directly. At each appointment, the different questionnaires will be administered, a physical examination will be performed that will include anthropometric measurements, and a second appointment will be made with the participant to perform a blood draw at their health center that same week. The research team will include a monitoring and management committee. It will review the quality of the data included in the database and will discuss any conclusions resulting from data of doubtful origin. Additionally, this committee will monitor recruitment rates, dropout rates, and any concerns related to the study. The reasons for dropping out, having made the appointment, or even the reasons for definitive non-participation will also be recorded. Participants and health professionals will be informed about these results. Figure 2 details the registration and evaluation schedule for this study, with dates included.

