Mental health disorders generate a great economic burden in the use of health system services and represent a significant proportion of health-seeking contacts in primary care (57, 58). In Spain, around 70–85% of the population opts for public primary health care over private insurance (59). Specifically, 60% of frequent users in primary health care suffer from some mental health problem, particularly depressive or anxiety disorders (60). Only 10% of patients with mental health problems seen in primary care are referred to mental health units (61). A World Health Organization report highlights the fundamental role of PHC personnel in the detection, diagnosis, and treatment of people with mental disorders (62, 63). The importance of the PHC lies in being the gateway to the health care system, its accessibility and its interaction with people with mental health problems and their families (61). Most people with mental health problems access primary care, and their disorders are more likely to be identified and treated appropriately and with less risk of stigma (62). In addition, the integration of mental health into primary care promotes comprehensive, coordinated, and person-cantered care for the many people with co-morbid physical and mental health problems (62).

Promoting the participation of the population in coping with diseases and their self-care and self-management of health is a key element in the health of the population in general and especially of the population with affective disorders (64). It is necessary to investigate further how people’s psychological constructs, beliefs and self-care capacity, as well as their lifestyles, can affect the well-being or discomfort of people and contribute to a healthier life from the perspective of mental health. Furthermore, it is important to assess longitudinal changes in these factors and affective disorders given their association with increased comorbidity and mortality (56). The analysis of the impact of psychological constructs and lifestyles on the mental health of individuals and communities will provide evidence that will make it possible to better address and prevent these prevalent problems as well as foster their improvement from a more global and holistic perspective.

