Finally, mediation/moderation analyses will be carried out to analyze whether psychological constructs participate as a mediator or as a moderator in the association of lifestyles (exposure) and anxiety, depression and/or addictions (outcome). The PROCESS analytical tool developed by Hayes will be used to assess mediation/moderation. These analyses were based on multiple linear regression path analysis (93). Bootstrap resampling (10.000 samples) will be used to estimate 95% confidence intervals. Given that heteroscedasticity is common in cross-sectional data, all analyses will include a correction for heteroscedasticity (HC0) (94). The Johnson-Neyman technique will be used to compute the range of significance and simple slopes for the interaction analyses (93). We will report unstandardized regression coefficients; all analyses will be two-tailed and used conventional significance thresholds (α = 0.05). Data collection and statistical analysis will be performed using Excel software, SPSS software (version 25.0) (95) and the statistical software environment R (version 3.6.2) (96).

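### Three recruitment routes feed one cohort checked only for eligibility and stratum, so representativeness is not supported and self-selection may bias the results

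*Protocol article*

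**What the plan says.** Section 2.4 of the protocol article sets cell targets by age band, sex and urban or rural residence. The stated purpose is variability and "reaching a maximum level of representativeness for the population". Section 2.5 then describes three ways into the cohort:

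- **Letter.** People obtained from the stratified sampling receive a letter and contact the research unit if they wish to take part.
- **Professionals.** Staff at the selected centres are given the unit's telephone number, to be used "if any patient that these professionals receive in their daily work is interested in participating in the study".
- **Media.** In addition, "broadcasting will be carried out through general media, posters, and press releases, which will raise awareness and obtain greater data".

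Interested people from any route meet the team. The team confirms the inclusion criteria and the stratum and takes consent. The article does not say that entry is limited to people on the letter list, and it describes no record of how a participant came in. Reasons for dropping out and for non-participation are recorded.

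Section 3.1 presents representativeness and extrapolation to other regions as strengths. It names low participation and withdrawal as the main difficulties, but not self-selection. The main objective (Introduction) is the association of psychological constructs with depression, anxiety and addictive behaviours, analysed in Section 2.7 by linear regression on continuous scores.

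**The concern.** Filling age, sex and area cells makes those three margins match the census. It does nothing about who, within a cell, comes forward. People who answer a poster, or who are seen often enough to be told of the study by a clinician, may differ from their neighbours in mood, help-seeking, patient activation or health literacy. Depression and anxiety are primary outcomes, and activation and health literacy are among the exposures.

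Two things are at stake. Statements about the population of Aragon, or about other regions, would rest on a sample whose composition on the studied variables is unknown. And if entry depends on both a construct and the symptoms, the regression coefficients that answer the main objective can be distorted within the sample. The article says that 60% of frequent users have a mental health problem ("60% of frequent users in primary health care suffer from some mental health problem"), which shows why recruiting through daily practice could matter.

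**Working it through.** **1. The plan's own figure.** Section 2.4 states: "Accepting an alpha value of 0.05 and a margin of error of 3% of units, the total sample size required was 290". That total already allows for 30% of participants dropping out. The prevalences given are "3.1% for major depression and 4.8% for anxiety disorders". The formula is n = z²p(1−p)/e². I take z = 1.96; two-sided testing is stated for the analyses in Section 2.7 ("all analyses will be two-tailed") and assumed here for the sample size. With e = 0.03:

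- p = 3.1%: n = 128.2, so 129; 129/0.70 gives 185.
- p = 4.8%: n = 195.0, so 196; 196/0.70 = 280.
- p = 5%: n = 202.7, so 203; 203/0.70 = 290.

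The stated 290 is therefore not reproduced exactly at 4.8% but is at 5%, probably through rounding. What matters here is that the 3-point margin describes sampling error only. It makes no allowance for how people enter.

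**2. Bias in a prevalence, frequent-attender scenario.** Inputs:

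- 60% affected among frequent users. The Discussion gives this figure for depressive or anxiety disorder; the Introduction words it more widely.
- At most 3.1% + 4.8% = 7.9% affected among everyone else. This is the sum with no overlap between the two disorders.
- f = share of the cohort made up of frequent attenders added beyond their normal share. The article does not give f, so it is assumed.

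Bias = f × (60 − 7.9) = f × 52.1 points:

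- f = 5%: 2.6 points
- f = 10%: 5.2 points
- f = 20%: 10.4 points

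The bias passes 3 points at f = 3/52.1, or about 6%.

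**3. Bias in a prevalence, milder scenario.** If the added participants have RR times the population prevalence p, then bias = f × p × (RR − 1). For anxiety, p = 4.8%, with f and RR both assumed:

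- f = 20%, RR = 2: 0.20 × 4.8 × 1 = 1.0 point
- f = 20%, RR = 3: 1.9 points
- f = 50%, RR = 2: 2.4 points
- f = 50%, RR = 3: 4.8 points

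The RR needed to reach 3 points is 1 + 3/(f × 4.8): 4.12 at f = 20% and 2.25 at f = 50%.

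**4. Associations.** No calculation is possible. The article gives nothing on how strongly entry by each route depends on constructs and symptoms, so neither sign nor size can be derived. The 3-point margin is a precision for a percentage and is no yardstick for a regression coefficient.

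**The case against.** The other side has several good points.

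- A reader might infer that volunteers are contaminating a random sample. The article describes the selection as stratified and never as random. The letter route is also opt-in, so the letter-invited group is itself self-selected. This stands.
- A reader might infer that the bias is known to exceed the stated margin. It is not: f and the excess of cases are unknown, and step 3 stays below 3 points in several settings. The 60% figure describes frequent users, whereas the professional route is open to any patient. Setting it against 4.8% would also compare depressive or anxiety disorder with anxiety alone.
- A reader might assume that the publicity is about mental health. Its content is not given, so selection on the outcome through media is a possibility only.
- Prevalence is not an objective. It drives the sample size and would appear only in the descriptive percentages of Section 2.7.
- Publicity could be read as encouraging response among people already invited, since Section 3.1 presents the letter and professional contact as ways to raise participation. The reference in Section 2.5 to any patient, and the aim of obtaining more data, speak against this reading. The text does not settle it.
- A route field and a sensitivity analysis might sit in a fuller document. That is fair, and their absence from the article is not the point. The point is that the article claims representativeness as a strength while describing recruitment that does not support it.

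**Conclusion.** The concern holds in a limited form. Three routes lead into one cohort, the stated entry check covers eligibility and stratum only, and self-selection is not among the limitations. The claims in Sections 2.4 and 3.1 are therefore unsupported beyond age, sex and area. That is weaker than saying that the cohort cannot be representative, which the article does not show.

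A prevalence estimate may be biased by more than 3 points. The illustrations run from 1.0 point (20% share, prevalence ratio 2) to 10.4 points (20% share of frequent attenders, 60% affected). All rest on assumed shares, and the milder ones also on an assumed ratio. The associations may be distorted, with direction and size unknown. This is an inexpensive improvement that changes what the study can conclude, not a flaw that invalidates it.

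**What to change.** 1. State whether entry is limited to people on the letter list.
2. If it is not, record the entry route (letter, professional, media) for every participant at enrolment. It may not be recoverable at the 5- and 10-year assessments.
3. Report response and baseline characteristics by route. A response rate needs a known number invited, so give counts where there is none.
4. Base any population statement on the letter-invited stratified sample, and say that it is also opt-in.
5. Repeat the main regression models in that subset as a sensitivity analysis. Do not present route as a covariate that removes the bias: if route depends on both construct and symptoms, adjusting for it need not help and may add bias.
6. Limit the representativeness wording in Sections 2.4 and 3.1 to age, sex and area, and add self-selection to the limitations.

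The cost is one extra data field, a less precise subset analysis and a less favourable claim.
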